## Abstract

**Background:**

Colorectal cancer is the third leading cause of cancer-related deaths in the United States. Despite the Healthy People 2030 goal of 70.5%, colorectal cancer (CRC) screening rates in Federally Qualified Health Centers (FQHCs) are suboptimal at about 40%. The Colorectal Cancer Awareness, Research, Education and Screening-Rural Expansion, Access, and Capacity for Health (**CARES-REACH**) study seeks to address this disparity and accelerate the adoption and utilization of effective, evidence-based CRC screening practices. This paper describes the CARES-REACH study design and implementation methods.

**Methods:**

Informed by a community-based participatory research (CBPR) framework and enriched by implementation science approaches, CARES-REACH features a stepped wedge design with extension for maintenance to support an implementation strategy focused on multiple levels: organizational, provider, and patient levels that entail processes to boost initial and repeat screening among average risk and age-eligible adults. This multilevel study entails the implementation of a core set of evidence-based interventions (EBIs) that include low literacy patient education (English, Spanish, and Haitian Creole language); provider education, system-wide electronic medical record (EMR) tools including provider prompts and patient reminders, FIT (fecal immunochemical test) kit distribution, plus an organization-wide cancer control champion who motivates providers, coaches and navigates patients, and monitors system-wide CRC screening activities.

**Trial registration:**

NCT04464668.

## INTRODUCTION

In 2023, approximately 153,020 new cases of colorectal cancer (CRC) were diagnosed in the United States (US), making it the third most common cancer diagnosed in both men and women (1). Regular screening of this detectable cancer offers an excellent opportunity to enhance the health outcomes of patients and community members, especially individuals who are underinsured or uninsured and being cared for in medical homes such as Federally Qualified Health Centers (FQHCs). The CRC screening rates in FQHCs are below both the national Health People targets (Healthy People 2020 target: 70.5% or Healthy People 2030: 74.4%). This lower performance may be attributed to a wide range of factors, such as lower rates of participation in screening due to unequal access or lack of health insurance, less access to screening/early detection and early treatment, and transportation obstacles, among others (2–6). Thus, the implementation of real-world interventions strategically placed in community-based clinics is needed to achieve a national goal of 80% in every community (7).

Both the US Preventive Services Task Force (USPSTF) and the American Cancer Society have recently updated recommendations for asymptomatic adults at average CRC risk from age 50–75 to age 45–75. Individuals at average CRC risk can be screened with multiple modalities, including annual stool-based tests (such as fecal immunochemical test [FIT]), or stool DNA tests [e.g., Cologuard] every three years, colonoscopy every ten years, CT colonography every five years, and/or flexible sigmoidoscopy every five years (8, 9). The use of FIT as a primary screening modality reflects a critical pragmatic approach, which is highly endorsed in low-resource environments such as FQHCs due to the limited availability of colonoscopy (10, 11). FIT is also often more accessible to geographically dispersed communities and at a lower cost (compared with colonoscopy) (12). In Florida, FQHC screening rates for patients aged 50–75 were 47% in 2019 and declined to 40% percent in 2020. Similarly, screening rates were 45% nationally in 2019 and dropped to 40% in 2020 (13, 14).

Recent studies, including our team’s preliminary investigations in community clinics (15–17), have demonstrated that CRC screening using a single-application FIT is well received by both patients and providers and can lead to initial screening rates of 80% (15–26). Our prior work has demonstrated high initial FIT uptake and endorsed the use of FIT paired with EBIs, such as videos, brochures, etc. (15–17, 27). Further, including coaches/navigators often increases patient engagement, mitigates obstacles, and serves as a way to bring resources for improving health outcomes for chronic diseases (54, 55). Attention to culture, literacy, and language (including English, Spanish, and Haitian Creole) to support CRC educational messaging is also a prerequisite for effective patient education. (56, 57, 58). The evidence-based interventions (EBIs) in CARES-REACH are based on characteristics and components that have been shown to be feasible and effective, such as using electronic health records (EHR) to identify patients needing screening and providing culturally, linguistically, and literacy-level-appropriate information in a clear manner (28). Evidence-based interventions, such as providing accessible FIT kits, have also been supported by several studies as an approach to removing access obstacles (10, 11, 29). Other effective educational EBIs include patient-directed videos, pamphlets, reminder letters/messages, and provider/nursing reminders and prompts (28).

FIT requires annual repeat testing to optimize clinical benefits (30–35), but repeat screening rates often decline sharply following initial screening (22%–60%) (19, 20, 36). This highlights the importance of implementing evidence-based intervention strategies to encourage both initial and repeat screening. However, multiple intersecting influences can impact the implementation of evidence-based practices in clinic settings. Strategies in prior studies were heavily led by the research team (15, 37–40); therefore, the next step is a more pragmatic trial with an implementation science-based approach. As such, a pressing gap remained to expand this work to broader geographically dispersed populations, including rural locations that may benefit from cancer screening. Therefore, our ‘real world’ implementation project, CARES-REACH, is intended to address this gap and assess intervention impact on annual FIT adherence over time.

The current paper describes the study protocol for the CARES-REACH intervention study, which is aimed to promote CRC screening among patients with medical homes at FQHCs, ages 45–75, and guided by implementation science approaches. The CARES-REACH study is a 5-year, multilevel intervention that leverages multiple evidence-based strategies and is fueled by community-based participatory research (CBPR) principles and community engagement approaches (15, 16, 41). In this paradigm, a Cancer Control-Implementation Advisory Board (CC-IAB) provides leadership and establishes decision-making procedures concerning the implementation of research activities by monitoring relevance, meaning, and overall practical utility. These perspectives are informed by our methodological research approach of **implementation science** whereby solutions for health disparities are gained through community and clinical member involvement, adding relevancy to the processes being implemented in ways that are salient, practical, scalable, and sustainable (42).

Selected constructs of the Reach, Effectiveness, Adoption, Implementation, and Maintenance (RE-AIM) framework (43) and Consolidated Framework for Implementation Research (CFIR) (44) further guide implementation evaluation of external and internal influences for this multilevel intervention to inform dissemination. RE-AIM constructs are used to characterize who is successfully reached by the intervention, the effectiveness of the intervention (uptake), adoption by the providers and system, implementation outcomes, and maintenance/sustainability.

The **scientific premise** of CARES-REACH is that an organization-wide multi-level CRC screening program can address persistent disparities in CRC mortality and screening rates, especially in FQHCs. The CARES-REACH study aims are as follows: (1) Implement an organization-wide multilevel CRC screening intervention plus a cancer control champion, (2) Explore whether practice settings and population characteristics impact annual CRC UDS screening rates, and (3) Conduct a comprehensive evaluation of the implementation process requirements, and intermediate patient screening outcomes. Study level components include Organization/Systems Level, Provider Level, and Patient level, with the Cancer Control Champion interacting at each intervention level. Various intervention strategies occur at each level and are depicted further in Table 1. The RE-AIM framework (43), and CFIR (44) guide implementation evaluation. **Findings** are expected to lead to a better understanding of the translation of research-tested intervention strategies in FQHCs and the processes that optimize (or hinder) intervention implementation under less controlled conditions.

## METHODS

### Study Design

Informed by implementation science and community-engaged approaches, CARES-REACH is a multilevel, multicomponent intervention featuring a stepped-wedge rollout and multilevel design (45, 46). The clinics (seven from each of the two Florida FQHC organizations) are randomized into two Waves (stratified by rural vs. urban location) and balanced by the number of patients 45–75 years [clinic volume] described in Table 2. Specifically, Wave 1 interventions were randomly selected to occur at four clinics in one FQHC organization. Then, precisely two of the four rural clinics, the smallest urban clinic and one of the two larger urban clinics, were randomly selected from that organization. An analogous approach was then used for the FQHC organization with four clinics in Wave 2 (three rural and four urban clinics). The CARES-REACH study supports implementing multiple strategies focused on the organizational, provider, and patient levels of influence to achieve the study aims described in Table 3.

### Setting

The setting for the CARES-REACH implementation is two FQHC organizations, which serve urban and rural regions in Central and Southwest Florida and provide care to diverse populations regardless of insurance status or ability to pay for services. The two FQHC organizations have each identified seven clinics, a mix of rural and urban-based clinics. Together, this allows us to assess whether the planned intervention has differential outcomes in two practice settings involving 14 clinics combined, with seven rural vs. seven urban clinics.

### Intervention Strategies

#### Organization/Systems Level:

We leverage existing EMR systems to support the patient-level intervention, laying the groundwork for future dissemination and implementation (18, 19, 47–52). The two clinic organizations use the same robust Athena Health Systems (Athenahealth^®^) EMR system, providing an exceptional opportunity to examine tracking features and capabilities as part of their organization’s response to National Committee on Quality Assurance (NCQA) and Patient-Centered Medical Homes requirements (53). These EMR systems allow for the collection of discrete data fields for CRC screening and related variables that can be directly downloaded (e.g., type of screening test, completion date, result). Essentially, three core components of the EMR systems can be leveraged to meet Aim 1: (1) the automated query feature to view screening status and results to identify and prioritize patients who are due for CRC screening; (2) documentation of discussion and ordering of CRC screening tests, and (3) automated calls, text messaging, and patient portals as ways to send patient reminders once patients receive an order for CRC screening (e.g., handed a FIT kit, or script/referral for colonoscopy).

### Provider Level

At the provider level, providers of various levels, including clinicians, nurses, and support staff, receive training offered by members of the research team in collaboration with the cancer control champion. Training topics included the importance of prioritizing CRC screening, current CRC guidelines, CRC screening options, use of the EMR to identify and track patients, delivery of compelling low-literacy screening messages, the importance of repeat screening, and EBIs (tools and resources). The cancer control champion also works directly with individual clinics and providers to support enhanced CRC screening intervention efforts.

### Patient Level

Providers deliver a core set of EBIs, including one-to-one patient education supported by low literacy/language-specific materials/media and recommending CRC screening (e.g., recommending FIT kit, Cologuard, or direct referral to colonoscopy as indicated). To best integrate this project into the workflow of the clinics, the core patient education intervention builds on existing and successful procedures for initial screening, repeat screening, and timely follow-up care, depending on screening modalities completed. When a FIT kit is provided, patients are instructed (in their preferred language) to collect the sample at home within 7–10 days and return (in person or by mail) to the clinic.

### Cancer Control Champion

A key component of CARES-REACH is the cancer control champion hired by each FQHC to work throughout the organization from a central location while leveraging the system-wide communication technology and the EMR. This centralized role expands the potential reach of CRC screening interventions, especially in settings such as FQHCs, where resources and efforts to improve cancer-related inequalities might be limited at individual clinic sites. The Cancer Control Champions have been hired and trained and bring backgrounds in healthcare, education, and/or nursing. Originally conceived as one person filling the role of champion, one FQHC organization has implemented a Champion Distributive Model whereby one individual is identified as the lead champion with other team members contributing supporting expertise such as quality improvement, outreach, or education.

Thus, the cancer control champion is pivotal to the CARES-REACH intervention at each of the three levels: 1) organization or systems level to prioritize CRC screening and optimize EMR systems for implementation of CRC screening; 2) provider education (initial and annual booster training) and feedback to support evidence-based CRC screening patient education, recommendation and distribution of FIT kits; and 3) patient level (coaching and addressing patient-specific barriers for individuals who do not return a FIT kit within 90 days of distribution). This latter level represents an approach supported by increasing evidence that is predicated on patient activation, education, and support for promoting both initial and repeat screening (15–26, 36, 54–57). Our evaluation efforts include understanding the infrastructure, resources, and processes for role sustainability.

For patients who receive a FIT kit or recommendation for other screening modality and have not completed any screening at 3-month EMR review, a coach intervention will be implemented by the cancer control champion. Coaching has been shown to increase engagement and improve outcomes (58). This component, delivered primarily by telephone (estimated 10 minutes), is a personalized modality intended to 1) assess the patient’s test-specific barriers; 2) assist patients in understanding the importance of repeat screening through education and use of materials; 3) coach the patient on personalized strategies to overcome their stated barriers; and 4) promote a sense of empowerment to use the information and complete a FIT screening. For individuals who continue to have questions or unresolved barriers, the coach will refer them to their provider for further management.

A multilevel approach to deliver EBIs using a stepped wedge design with one year of observation is being employed to observe secular trends followed by a sequential roll-out of the intervention using two waves, allowing for an extension of at least two years after intervention initiation, which allows for assessing screening maintenance. The stepped wedge approach aims to accelerate the rollout of EBIs in “real world” practice settings while capturing the added effect of a Cancer Control Champion. The multilevel approach expedites the successful transfer of an intervention to other settings as the design is intended to disentangle contextual factors that may affect optimal implementation. The main outcome assessed is a change in annual screening rates (all screening modalities), and secondary measures include sustained maintenance.

CFIR is a determinant framework focused on settings, barriers, and facilitators. Therefore, CFIR constructs that inform the current study include external CRC screening benchmark requirements, organizational readiness, compatibility, patient characteristics, adopter [provider, clinic] characteristics, engagement, cost, and cancer control champion involvement (44).

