## Figures and Tables

**Figure 1 F1:**
[figure not shown]
Legend not included with this version.

**Table 1 T1:** Intervention Strategy Examples

Level	Intervention Strategy Examples
**Organization**	Optimizing EMR Processes (Automated Queries, Flags, provider/nursing prompts and reminders, etc.)
	Automated Calls, Texts, Patient Portals- messages sent to Patients about CRCS (Recipient = Patients)
	Wave 1 Clinics Activated - intervention implementation at all three levels.
	Wave 2 Clinics Activated - intervention implementation at all three levels.
	Readiness Evaluation Assessment Level (REAL) Survey Measure – at baseline and repeated at the midpoint and end of the implementation
	CRC Awareness Activities (i.e., CRC awareness month, promotional items, etc., throughout the project period)
**Provider**	Initial Provider Education (physicians, nurses, staff) – by wave of stepped-wedge and rollout design
	Annual Booster Education – by wave of stepped-wedge and rollout design
	Providers engaging with Champion (e.g., CRC screening scorecards)
	REAL Survey Measure (baseline and repeated at midpoint and end of implementation)
**Patients**	Dissemination of Language-Specific Educational Materials (Recipient: Patients)
	Patients Receive FIT kits (and other appropriate screening modalities) Coaching of patients who do not complete prescribed screening: From Champion (at 30 days or as needed; (Recipient = Patients)
**Champion**	Champion Hire/trained. 1 Champion for each FQHC/Organization level
	Assist in Educating and Training Providers (Physicians, Nurses, Medical Assistants, staff) (Target: Providers)
	Assist in Optimizing EMR (Target: Organization)
	Identify Patients who don’t return FIT (Recipient: Patients)
	Coach Intervention and Navigate Patients (Recipient: Patients)
	Organizational Change Agent (Recipient: Organization, Provider, and Patient Levels) Assist in identifying patients needing screening (EMR/Organization and provider levels) and identify individual patients needing coaching (patient level)
	REAL Survey Measure (repeated from baseline, midpoint, and end of project implementation

**Table 2 T2:** Stepped Wedge Design with Extension for Maintenance:

	Year 0 Baseline	Year 1 Wave 1	Year 2 Wave 2	Year 3 Sustaining	Year 4 Evaluation
Features/Aim	(Pre-Intervention)	Initiation	Initiation	Implementation	
**Number of Clinics**	0/14	7/7	14/0	14/0	14/0
**Exploration of EMR Optimization**	Yes	Yes	Yes	Yes	Yes

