**Provider Education and EBIs for Patients**	N/A	Yes	Yes	Yes	Yes
**Coach Intervention**	N/A	Yes	Yes	Yes	Yes
**Annual Provider Booster Education**	N/A	N/A	Yes	Yes	Yes

**Table 3 T3:** CARES-REACH Aims

	Aim	Expected Outcomes
**Aim 1**:	Implement an organization-wide multilevel CRC screening intervention using evidence-based interventions (EBIs) and an organization-wide cancer control champion in FQHCs in rural and urban Central and Southwest Florida.	The primary outcome measured is the change in annual CRC screening rates (UDS) at the organization and intervention clinic sites, among other screening uptake behaviors.
**Aim 2**:	Explore whether practice setting (rural vs. urban) and population characteristics (e.g., nativity [foreign-born status], language preference, education, income, health insurance, etc.) may differentially impact annual clinic CRC UDS rates and other screening outcomes.	Patient de-identified data will be pooled for analysis. This method will be useful in determining whether or not differences can be attributed to factors outside of the typical clinical setting. This aim is to explore disparities by geography and population characteristics.
**Aim 3**:	Conduct a comprehensive evaluation of the implementation process, resource requirements, and intermediate patient screening outcomes of the CARES-REACH program in FQHCs.	To achieve this objective, we will undertake a comprehensive evaluation of the CARES-REACH program (facilitators/obstacles) to inform and guide program adjustments and upgrades at the two existing FQHC systems. If these assessments successfully yield informative data, more community and FQHC locations may be able to implement the CARES-REACH program thanks to this method (scale-up).

**Table 4 T4:** Multi-Level Activities

Champions		

Complete REAL survey (baseline, midpoint/ first follow up, second follow up). Assist in the Education and training of providers. Assist in the optimization of EMR for CRC screening. Identify patients who do not return the FIT Kit Coach and navigate patients. Provide feedback to patients and providers. Serve as Organizational change agent for cancer screening. Facilitate activities at Organization/Systems, Provider, and Patient levels.		

Organization/Systems	Provider	Patient

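### The stepped wedge cannot capture the champion's added effect: champion coaching and the EBIs start together at each wave, so the randomized contrast gives only the effect of the bundle

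*Protocol article*

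**What the plan says.** The design paragraph under Methods, Cancer Control Champion, gives the stepped wedge two purposes: faster rollout of the EBIs, "while capturing the added effect of a Cancer Control Champion".

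The design itself is laid out elsewhere in the article:

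- **Activation.** Table 1 lists "Wave 1 Clinics Activated - intervention implementation at all three levels", with a matching line for Wave 2.
- **Timing.** In Table 2 the rows "Provider Education and EBIs for Patients" and "Coach Intervention" have the same pattern: not applicable in Year 0, Yes in Years 1 to 4. The row "Exploration of EMR Optimization" is Yes in every year and is not split by wave.
- **Reach.** The champion is "hired by each FQHC to work throughout the organization from a central location". Table 1 gives one champion per organization, and the text adds that one organization uses a lead champion with a supporting team. The Abstract's Methods describe "system-wide electronic medical record (EMR) tools including provider prompts and patient reminders".
- **Randomization.** Study Design randomizes clinics within each of two organizations (seven clinics each), so both waves are present in both organizations.
- **Analysis.** Statistical and Data Analysis fits 14 × 3 = 42 annual clinic rates with terms for intervention, clinic, rural location and time. The power figures (83.6% for 4 points, 97.5% for 5 points) compare intervention with non-intervention clinics.

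**The concern.** To estimate what a champion adds to the EBIs, the design needs some clinics or periods with the EBIs and no champion, or the reverse. If the two always start together, their effects can be estimated only as a sum. The Discussion looks ahead to extending the champion model beyond colorectal screening and to informing organizations and policymakers. A positive Aim 1 result reported alongside the added-effect wording could be credited to the champion when the data cannot separate the champion from provider education, patient materials, FIT distribution and EMR tools.

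A second and weaker issue is the comparator. One champion role and one EMR serve activated and not-yet-activated clinics in the same organization. If organization-level work reaches Wave 2 clinics during Year 1, the contrast measures activation over a partly exposed comparator, which is less than the full organization-wide programme named in Aim 1.

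**Working it through.** **1. Count the clinic-years.** The article does not name the three years behind the 42 rates. I take Years 0 to 2, the years in which Table 2 shows the rollout.

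| | Year 0 | Year 1 | Year 2 | Total |
|---|---|---|---|---|
| Activated (EBIs and coaching) | 0 | 7 | 14 | 21 |
| Not activated | 14 | 7 | 0 | 21 |
| EBIs without champion coaching | 0 | 0 | 0 | 0 |

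The zero in the last row holds for any choice of three years, because the two Table 2 rows are identical throughout. Table 2 has no separate champion row, so the coaching row is the only dated evidence of when champion work starts.

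**2. Check identifiability.** Write the design matrix for the 42 rates with 14 clinic columns, 2 time columns and 1 intervention column: 17 columns, rank 17, so the bundle effect is estimable. Now add a champion column.

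- *Champion starts with activation.* The column equals the intervention column: 18 columns, rank 17. The champion effect is not estimable.
- *Champion active in every clinic from Year 1.* The column equals the sum of the Year 1 and Year 2 columns: 18 columns, rank 17. The champion effect is aliased with time.

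On either reading no champion effect can be separated. Treating clinic as random, as the model does, changes nothing, because neither dependence involves the clinic columns.

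**3. What sharing would do to the contrast.** Let the bundle effect be δ, and let Wave 2 clinics receive a fraction f of it in Year 1. Net of common time effects, the expected shifts are:

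| | Year 0 | Year 1 | Year 2 |
|---|---|---|---|
| Wave 1 | 0 | δ | δ |
| Wave 2 | 0 | fδ | δ |
| Difference | 0 | (1 − f)δ | 0 |

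The model fits a wave difference of 0, θ, 0, so the expected estimate is θ = (1 − f)δ. Anything common to all clinics in a given year, such as EMR work from Year 0, cancels in the difference row.

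**4. Illustration on the plan's power scale.** The stated power cannot be reproduced directly, because the article gives neither patients per clinic-year nor alpha. Assuming two-sided alpha 0.05 and a normal approximation, 83.6% power at 4 points implies a standard error of 4 / (1.960 + 0.978) = 1.361 points. That standard error gives Φ(5/1.361 − 1.960) = 95.7% at 5 points, against the stated 97.5%, so the two figures are roughly compatible. Both describe the bundle.

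For a true effect of 4 points, power = Φ(4(1 − f)/1.361 − 1.960):

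| f (assumed) | Expected estimate (points) | Power |
|---|---|---|
| 0 | 4.0 | 83.6% |
| 0.1 | 3.6 | 75% |
| 0.2 | 3.2 | 65% |
| 0.3 | 2.8 | 54% |
| 0.5 | 2.0 | 31% |

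No value of f can be taken from the article. The table shows sensitivity only; it does not estimate what happened.

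**The case against.** The strongest reply is that little rests on the phrase. It is one narrative clause. Aim 1 is stated as the intervention plus a champion, the model has one intervention term, and no hypothesis or power figure concerns the champion alone. The planned analysis is therefore already an analysis of the bundle. That stands, and it limits the point to what the trial may claim. It does not rescue the clause, which assigns to the design a property it lacks and which no analysis plan could supply. Reading the added effect as champion over usual care does not help either, since the study EBIs start at the same step.

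Three stronger readings are tempting, and the document does not support them:

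- *Control clinics already receive part of the programme.* A reader might infer this from the system-wide EMR tools and the champion's organization-wide remit. Those passages describe reach, not Year 1 timing. Table 1 points to switch-on by wave and delivers provider education by wave. Nothing says that prompts, scorecards or coaching reached Wave 2 clinics in Year 1. Sharing is a plausible risk, not an established fact.
- *EMR work marked Yes from Year 0 dilutes the effect.* The row concerns exploration of EMR optimization, which need not mean tools in use, and work common to all clinics is absorbed by baseline and time. Only Year 1 gains that reach Wave 2 clinics would shrink the contrast.
- *No analysis can say anything about the champion.* This is too absolute. Table 5 tracks who receives coaching, and individual-level data are planned, so a non-randomized description is possible. The limit applies to randomized contrasts.

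A condensed article may also leave clinic-level switch-on rules to the full protocol, so their absence is not held against it here.

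**Conclusion.** The added-effect claim is wrong as stated and should be corrected. No randomized contrast in this design separates the champion from the EBIs: 0 clinic-years have the study EBIs without champion coaching, and a champion term is aliased with either intervention or time. This rests only on Tables 1 and 2 and the stated model, with the coaching row standing for the start of champion work. Aim 1 remains analysable as the effect of the activated bundle.

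Sharing of organization-level activity with Wave 2 clinics in Year 1 is a risk that follows from randomizing clinics within organizations. If it occurred, it would shrink the estimate to (1 − f) of the bundle effect, with f unknown. The power values above depend on assumed f, on two-sided alpha 0.05 and on the back-solved standard error, and should not be quoted as expected power.

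**What to change.** 1. Delete the added-effect clause from the design paragraph.
2. Define the Aim 1 effect, for example: *the effect of activating the full package (provider education, patient EBIs and champion coaching) in a clinic, relative to concurrent clinics not yet activated, which may share organization-level EMR and champion activity. The design does not separate the champion's contribution from that of the other components.*
3. Limit any champion-specific statement to descriptive, non-randomized analysis, and label it so.
4. Report champion contact, coaching and EMR-tool exposure by clinic and year, including Wave 2 clinics in Year 1, so that readers can judge how far the comparator was exposed.

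Restricting EMR tools to activated clinics until Wave 2 starts is no longer an option, because the Discussion says both waves have been initiated.

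The cost is a change of wording and one exposure table. The article already plans process tracking, champion-interaction records and the Table 5 counts of coaching and EMR enhancements. It does not say that these are held by clinic, so some may need a clinic identifier and a date added. The downside is a narrower claim about the champion.
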